### Fidelity and supervision

Group facilitators will provide supervision by phone on a bimonthly basis, and three face-to-face supervision meetings after each fidelity check. Supervision will be conducted by clinical staff who have extensive knowledge of the 4Rs and 2Ss model, and who have supervised clinicians in other initiatives using this model. Additionally, two independent raters will conduct fidelity checks for a minimum of three sessions to ensure adherence to the treatment model. As fidelity checks will be conducted by two personnel, inter-rater reliability will be computed. Providers falling below 80% in fidelity will be given additional supports, such as additional supervisory sessions, to improve adherence.

### Clinic involvement

Of the approximately 134 clinics that will be invited to participate; 37 clinics have been enrolled in the study thus far. Data collection has begun at 14 clinics in the SAU clinic, eight clinics in condition 1 and seven clinics in condition 2. Others have agreed to participate and data collection will begin shortly.

### Measures

Data collection will occur at baseline, 8, and 16 weeks from baseline, and at 6-month follow-up. Demographic characteristics about familial factors (e.g., age, race/ethnicity, family income) will be collected via a questionnaire used in prior studies. A separate demographic questionnaire will be administered to providers to gather information including their age, race/ethnicity, education, and credentials.

### Child factors

#### Child oppositional defiant disorder

will be measured by the Disruptive Behavior Disorders Rating Scale Oppositional Defiant Subscale [38]. Completed by the child’s caregiver, this subscale consists of eight items that are ranked using a 4-point Likert scale ranging from “not at all” (0) to “very much” (3). Total scores range from 0 to 24, and a total of four or more items endorsed as “pretty much” or “very much” are needed to meet criteria for ODD. Two studies that used this scale across several outpatient mental health clinics within NYC found good internal consistency with a Cronbach’s *α* at baseline of .70 and .89, respectively [39].

Child ODD will also be measured by the Iowa Conners Rating Scale-Oppositional/Defiant Subscale (IOWA CRS OD) [40], a widely used brief measure of oppositional defiant behavior in children. Completed by the child’s caregiver, the IOWA CRS OD includes items ranked using a 4-point Likert ranging from “not at all” (0) to “very much” (3). Total scores range from 9 to 30, with higher scores indicating greeter severity of symptoms. A previous randomized effectiveness study of the MFG intervention found that this scale had good internal consistency with a Cronbach’s *α* at baseline of .86 [39].

#### Functioning

Child functioning will be measured via the Impairment Rating Scale (IRS), [41] a six-item instrument that asks caregivers to rate the severity of their child’s problems and need for treatment across functional domains, including their relationship with peers, parent(s), and sibling(s); academic progress, and family functioning. Caregivers place an “X” on a 7-point scale to signify their child’s functioning along a continuum of impairment that ranges from 0 (no need for treatment) to 6 (extreme need for treatment). Scores of three or greater indicates clinical impairment [42]. The IRS has shown evidence for concurrent, discriminant, and convergent validity, and acceptable levels of temporal stability [43].

### Caregiver factors

#### Depression

Caregiver depression will be measured using the short form of the Center for Epidemiologic Studies Depression Scale (CESD) [44-46], a free, publically available screening tool consisting of seven items that assesses the frequency of depressive symptoms within the past week. Items are anchored on a 4-point Likert scale ranging from 0 (rarely/none of the time) to 3 (most or all of the time). CESD scores range from 0 to 21, with a score of 8 and above considered clinically significant depressive symptoms [45]. The CESD short form evidences high internal consistency, with a Cronbach *α* of above 0.8 [45]

#### Stress

The Parenting Stress Index (PSI) short form will be administered to measure stress [47]. This 36-item scale uses a 5-point Likert scale, ranging from “strongly disagree (1)” to “strongly agree (5).” Total scores range from 36 to 180, with higher scores indicating increased levels of parent stress [48]. In a prior study of the 4Rs and 2Ss MFG, Cronbach’s *α* values reported as baseline, mid test, post test, and 6-month follow-up, were 0.91, 0.92, 0.94, and 0.94, respectively [39].

### Family factors

#### Parenting quality

The Alabama Parenting Questionnaire (APQ-9) short form will measure parenting factors, and specifically positive parenting, inconsistent discipline, and poor supervision [49]. This scale consists of nine items that are measured in terms of frequency, ranging from never (1), to always (5). Items are summed to determine positive parenting, inconsistent discipline, and poor supervision. The APQ-9 short form was shown to be reliable and valid in two prior studies, and has a Cronbach’s *α* ranging from 0.59 to 0.84 in the first study and 0.80 to 0.92 in the second study [49].

#### Uptake of the 4Rs and 2Ss MFG

Two subscales of the McMaster Family Assessment Device (FAD) [50] will measure the extent to which the 4Rs are used within the family. The two subscales, focusing on roles and communication, use a 4-point Likert scale ranging from strongly disagree (1) to strongly agree (4). Higher numbers indicate more problematic functioning. The FAD was shown to have strong validity in multiple studies, and a test of this scale using a sample of 503 individuals found acceptable reliability of the subscales, with a Cronbach’s *α* of 0.72 (Roles) and 0.75 (Communication) [50].

#### Social support

To measure social support, the family subscale of the Multidimensional Scale of Perceived Social Support (MSPSS) [51] will be administered. This four-item subscale, uses a 7-point Likert scale ranging from very strongly disagree (1) to very strongly agree (7). Scores are summed, with higher scores reflecting greater perceived support.

The MSPSS has strong factorial validity as well as good internal and test-retest reliability (Cronbach *α* = 0.85 for the Family subscale) [51].

#### Engagement in treatment

Attendance will be collected, and a total number of sessions attended will be tallied for each participant.

#### Barriers to treatment

These will be assessed using the Kazdin Barriers to Treatment (KBT) scale [52], which is comprised of three subscales: perceived relevance of treatment, relationship with the therapist, and critical events. The first two subscales consist of 14 items combined, and are rated on a 5-point scale, ranging from (1) never a problem to (5) very often a problem. The third subscale, delivered in a yes-no format, includes 14 critical events that may lead to treatment termination. Items on the 5-point scale are summed to provide the total barriers score, and items on the binary scale (1 = no, 2 = yes) are summed to reflect the absence or presence of critical events [52, 53]. Higher scores reflect greater severity regarding barriers to treatment [52].

### Implementation processes factors

#### Attitudes about evidence-based practices

The Evidence-Based Practice Attitude Scale [21] will assess provider attitudes toward evidence-based practices. The scale is comprised of four subscales: the intuitive *appeal* of EBP, the likelihood of adopting EBP in light of such *requirements*, *openness* to new practices, and the degree to which *divergence* is perceived between usual practice and research-based/academically developed interventions. Five possible responses are provided on Likert scale, from 0 (not at all) to 4 (to a very great extent). For each subscale, a mean score is calculated and the fourth (divergence) is reverse coded. A higher mean score indicates a greater degree of the construct reflected by that subscale. A study using this scale to assess service provider attitudes from 51 mental health service programs found good internal consistency reliability, with an overall Cronbach’s of 0.77 [21].

#### Organizational processes and readiness to change

This will be assessed via the Texas Christian University (TCU) Organizational Readiness for Change (TCU ORC) instrument [54]. Responses to this 66-item instrument range from strongly disagree (1) to strongly agree (5). Subscales focus on motivation for change, resources, and staff. In addition, the Training Exposure and Utilization subscale measures training exposure and utilization within an agency. It contains seven items that are assessed on a scale that ranges from never (1) to almost always (5). Mean scores for each subscale are multiplied by 10, so that final scores range from 10 to 50. Scale scores above 30 indicate some average agreement on the concept measured by the scale, and scale scores below 30 indicate some disagreement on average [55]. Reliability and validity of the ORC were examined in a study using a national sample of over 500 staff members from more than 100 programs, with the majority of subscales showing a Cronbach’s *α* of above .70 [54].

#### Beliefs about treatment

The Measure of Beliefs about Participation in Family Centered Service Delivery [56] will assess providers’ beliefs about participating in family centered services. This 28-item instrument consists of five scales that measure beliefs about family centered philosophy and principles, positive and negative outcomes, personal competencies, and barriers [56]. Responses are provided on a 7-point scale ranging from strongly disagree (1) to strongly agree (7). The total scale score is calculated as the average of all means of the scale scores. Higher scores on scales represent stronger beliefs regarding family centered services. A study examining the development and validity of this instrument using 818 respondents showed good evidence of construct validity for this measure as well as moderate to excellent reliability, with coefficient *α* values ranging from .61 to .83 [56].

#### Treatment fidelity and supervision

Fidelity monitoring tools will assess facilitator adherence to curriculum content (e.g., session topic, information conveyed, competence in guiding discussions) and clinical skills (i.e., active listening). These fidelity assessments were standardized during fidelity observations of prior 4Rs and 2Ss MFGs studies [1, 18].

#### Organizational characteristics

These include size, fiscal health and funding streams, and populations served will be analyzed from two pre-existing datasets collected by New York State Office of Mental Health (NYSOMH) about organizational composition and service delivery.

### Hypotheses and data analytic strategy

The purpose of this study is to examine outcomes associated with the 4Rs and 2Ss MFG, implementation processes that impact uptake and sustained use of the intervention over time, and the impact of an innovative change agent team upon outcomes. The following hypotheses will be tested:
*Aim #1*: to examine the short-term and longitudinal impact of 4Rs and 2Ss MFG on child ODD and functioning
*Hypothesis #1*: youth who participate in 4Rs and 2Ss MFG will display significantly reduced conduct difficulties and increased functioning over time compared to those involved in standard care: youth in the 4Rs and 2Ss MFG + CIT condition will evidence the greatest magnitude of change in outcomes over time
*Aim #2*: to examine family level mediators (e.g., parenting, family process) of child outcomes
*Hypothesis #1*: based on existing 4Rs and 2Ss MFG findings, specific family level variables (caregiver stress, the parent/child relationship and established rules) will be associated with significantly greater impact on child outcomes over time relative to social support, established responsibilities, and respectful communication
*Aim #3*: to examine clinic- (readiness to adopt an innovation, leadership support, and climate) and provider-level moderators (engagement, preparedness, motivation) of 4Rs and 2Ss MFG implementation and integration
*Hypothesis #1*: leadership support will evidence significantly greater impact on 4Rs and 2Ss MFG implementation/integration in comparison to general readiness and clinic climate
*Hypothesis #2*: provider motivation will evidence significantly greater impact on 4Rs and 2Ss MFG implementation/integration relative to other provider-level variables
*Aim #4*: to examine the impact of CITs on clinic- and provider-level moderators of 4Rs and 2Ss MFG implementation and integration
*Hypothesis #1*: clinic directors assigned to MFG + CIT will evidence significantly higher readiness for innovation and support, and providers assigned to MFG + CIT will evidence significantly higher preparedness and motivation to implement MFG relative to MFG alone
*Hypothesis #2*: preparedness, motivation of providers, and leadership support assigned to MFG + CIT will be maintained over time and be significantly higher relative to MFG alone
*Hypothesis #3*: providers assigned to MFG + CIT will evidence significantly enhanced fidelity to MFG relative to MFG only
*Hypothesis #4*: clinics assigned to MFG + CIT will have more MFGs initiated and completed (with high fidelity and attendance) relative to MFG alone

Overall, the two primary outcomes being tested in this study are changes in child behavior and child functioning. These outcomes are being tested specifically in aims 1 and 2, as measured by the Disruptive Behavior Disorders Rating Scale Oppositional Defiant Subscale [38], Iowa Conners Rating Scale-Oppositional/Defiant Subscale [40] and the Impairment Rating Scale (IRS) [41]. Aims 3 and 4 intend to measure mediators of the primary outcome, by testing clinic readiness and motivation to implement the 4Rs and 2Ss intervention initially and over time, and testing whether fidelity has been adhered to.

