### The 4Rs and 2Ss Multiple Family Group (MFG) intervention

The 4Rs and 2Ss Multiple Family Group (4Rs 2Ss MFG) for Strengthening Families Program is an evidence-based, manualized, family based treatment for families of children with disruptive behaviors [10–15]. Recently listed on the Substance Abuse and Mental Health Services Administration (SAMHS) National Registry of Evidence-based Programs and Practices [16], this model is associated with high attendance rates, improvement in behavior problems, caregiver depression and stress among predominantly low-income, minority families [14].

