### Conceptual model

The 4Rs and 2Ss MFG intervention draws from group therapy techniques, systemic family therapy, and behavioral parent training [12]. It was developed using a common elements approach [10], which entails identifying techniques and procedures that are common to already existing evidence-based protocols for specific problem areas [17]. As such, the 4Rs and 2Ss MFG integrates family processes and parenting skills linked to conduct problems from the empirical academic literature [10, 14]. The targeted skills and processes are referred to in the curriculum as the 4Rs (Rules, Responsibility, Relationships, and Respectful Communication) and 2Ss (Stress and Social support) [14]. Additionally, families of youth with DBDs and mental health providers assisted in the model’s development specific to enhancing cultural and contextual relevance of the intervention content, as well as engagement [10].

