**Fig. 2 Fig2:**
[figure not shown]
Analysis of mechanisms

We will employ mediation analysis with two-level MSEM models as explicated by Preacher, Zhang and Zyphur [57] and extended to three-level models by Preacher [57]. We will use a combination of limited information estimation frameworks (focused on sub-portions of the full model) and full information estimation frameworks (focused on the entire three-level model) to strategically answer questions. At level 1, child outcomes at the immediate post test are modeled as a function of the family predictors (see Fig. 2) using baseline measures of outcomes and family mediators as covariates, taking into account the clustering at the higher levels of the model. The follow-up (6-month) measures of the mediators and the outcomes are included within the model in a classic SEM panel model with autoregressive effects, thereby linking the follow-up data to the immediate post-test data. This is an advantage of using MSEM over traditional multi-level modeling. Different centering strategies (e.g., grand mean versus group mean) can be explored to garner various perspectives on the data. This feature of the model provides perspectives on aim 2 and the relative importance of paths g–l in Fig. 1. To ascertain perspectives of the effects of clinic-level variables on provider variables, random intercept MSEM with the provider-level variables can be estimated as a function of the clinic variables that include dummy coded treatment variables (4Rs and 2Ss MFG + CIT versus 4Rs and 2Ss MFG) impacting the clinic mediators of readiness, leadership support, and climate, which in turn, affect the provider-level intercepts. This modeling, or variants of it, address aims 3 and 4.

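### The Aim 2 ranking gives caregiver depression no stated role, so the path and relative weight of caregiver stress may absorb part of any depression effect

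*Protocol article*

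**What the plan says.** All references are to the protocol article.

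- **Hypotheses and data analytic strategy, Aim 2, Hypothesis 1:** "specific family level variables (caregiver stress, the parent/child relationship and established rules) will be associated with significantly greater impact on child outcomes". The three comparators are responsibilities, communication and social support. That is three variables set against three.
- **Analytic strategy, text following Fig. 2:** the level-1 model is said to give "perspectives on aim 2 and the relative importance of paths g–l in Fig. 1". The letters g to l are six paths. The stated adjustment is for baseline values of the outcomes and of the family mediators. Importance is then ranked by relative weight analysis.
- **Conceptual model:** the curriculum targets are the "4Rs (Rules, Responsibility, Relationships, and Respectful Communication) and 2Ss (Stress and Social support"). The six Aim 2 variables are these six targets.
- **The 4Rs and 2Ss Multiple Family Group (MFG) intervention:** the model is associated with "improvement in behavior problems, caregiver depression and stress among predominantly low-income, minority families".
- **Depression (under Caregiver factors):** "Caregiver depression will be measured using the short form of the Center for Epidemiologic Studies Depression Scale". The Parenting Stress Index follows in the same group of measures.
- **Child factors:** both ODD scales and the Impairment Rating Scale are completed by the caregiver.

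No hypothesis and no sentence of the analytic text uses the depression score.

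**The concern.** Aim 2 asks which family variables matter most for the child. Even where arms are randomised, the level of stress or support a family reaches is not, so each mediator-to-outcome path is an observational regression. It is confounded by anything that is related to both the mediator and the outcome and is absent from the model.

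Depression is a plausible candidate on the article's own account. It is reported to improve with the intervention, in the same sentence as stress. It comes from the same caregiver who reports the stress and rates the child, so it could act through real influence on the child or through the rating. Relative weights depend on which predictors are entered, so a distortion of the stress path passes into the ranking.

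At stake is how the place of stress in Aim 2 is read: as an effect of parenting stress, or as a mixture of stress and depression that the planned model cannot separate.

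**Working it through.** **Step 1: count the paths.** g, h, i, j, k, l = 6. The hypothesis names 3 + 3 = 6 variables, and the 4Rs and 2Ss are 4 + 2 = 6. The count closes and leaves no path for depression. The figures themselves cannot be checked.

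**Step 2: the formula.** On standardised variables, leaving depression out of the six-variable model changes the stress coefficient to

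b\* = b_stress + b_dep × d,

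where d is the slope on stress when depression is regressed on all six mediators.

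**Step 3: inputs, all assumed.** The article gives no correlation and no effect size. For illustration:

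- each of the six mediators has a true coefficient of 0.15;
- the mediators correlate 0.3 with each other;
- depression correlates 0.2 with the five mediators other than stress, and r with stress;
- all scores point in the same direction.

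Inverting the six-variable correlation matrix gives

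- for stress, d = (0.88r − 0.12)/0.7;
- for each other mediator, d = (0.08 − 0.12r)/0.7.

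Example with r = 0.5 and b_dep = 0.2: d = (0.44 − 0.12)/0.7 = 0.457, so b\* = 0.15 + 0.2 × 0.457 = 0.241. For another mediator, d = (0.08 − 0.06)/0.7 = 0.029, so b\* = 0.156.

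**Step 4: range.** The last two columns give the relative weight of stress divided by that of another mediator with the same true coefficient.

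| r (stress, depression) | b_dep | stress coefficient, six variables | other coefficient, six variables | weight ratio, six variables | weight ratio, seven variables |
|---|---|---|---|---|---|
| 0.2 | 0.2 | 0.166 | 0.166 | 1.00 | 1.00 |
| 0.3 | 0.2 | 0.191 | 0.163 | 1.17 | 1.07 |
| 0.5 | 0 | 0.150 | 0.150 | 1.00 | 0.91 |
| 0.5 | 0.2 | 0.241 | 0.156 | 1.57 | 1.21 |
| 0.7 | 0 | 0.150 | 0.150 | 1.00 | 0.81 |
| 0.7 | 0.2 | 0.292 | 0.149 | 2.04 | 1.36 |
| 0.7 | 0.3 | 0.363 | 0.148 | 2.63 | 1.68 |

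With CESD in the model, the stress coefficient is 0.15 in every row.

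**Step 5: reading the table.**

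- If depression has no effect beyond the six mediators (b_dep = 0), the stress coefficient is unbiased.
- If depression correlates equally with all six (r = 0.2 here), every coefficient rises alike and stress gains no rank.
- Stress is favoured only when both conditions fail. It then takes a fraction of the depression effect, not all of it.
- The seven-variable weights are not neutral either. With b_dep = 0 the stress ratio falls to 0.91 or 0.81, because relative weights share joint variance among correlated predictors. The path coefficient should therefore be reported beside the weights.

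**Step 6: precision cost of adding CESD.** If stress and depression correlate 0.6 given the other predictors (assumed), the variance inflation is 1/(1 − 0.36) = 1.56. Its square root is 1.25, so the standard error of the stress path grows by about 25%.

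**The case against.** **The six variables are the stated question.** Aim 2 compares the components of the curriculum, and depression is not one of them. This stands as the reason for ranking six variables. It does not make their paths free of confounding by a seventh.

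**The model cannot be seen in full.** The article refers to Fig. 2 for the family predictors, and an article may leave a full covariate list to the protocol or analysis plan. This stands, and it limits the point to what the text shows: a ranking set of six and a stated baseline adjustment, neither of which names depression.

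**Baseline adjustment already helps.** Adjusting for baseline outcomes and mediators should absorb much of a stable tendency to report both more stress and worse behaviour. It does not deal with change in depression during treatment, which is what the article reports for the intervention.

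**Depression may follow from stress.** In that case CESD at the same wave lies on the path from stress to child outcome, and adjusting for it removes part of a real stress effect. This stands. It is why the model with concurrent CESD should not alone decide the hypothesis.

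**A stronger reading goes too far.** A reader might infer that stress is the predicted winner of Aim 2, that it is in fact credited with the effect of depression, and that the hypothesis can be confirmed when stress has no effect of its own. The article supports none of these. Stress is one of three variables predicted to lead, and inflating it does nothing for the parent/child relationship or rules, which must also exceed the comparators. Depression may equally correlate with perceived family support or communication, which would raise those paths instead. A reader might also set the shift against a standard error of 1/√2688 = 0.019. That figure ignores clustering within clinics and the correlation among mediators, so it cannot be used to call the shift highly significant.

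**Conclusion.** The point holds in limited form. As far as the text shows, a measured caregiver variable that the article says improves with the intervention has no role in the Aim 2 ranking, and the stress path is open to confounding by it. Whether this happens, and by how much, is unknown.

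Under the assumptions shown (r of 0.3 to 0.7, depression effect of 0 to 0.3), a true stress coefficient of 0.15 appears as 0.15 to 0.36. With an effect of 0.2, the weight of stress relative to an equally strong mediator appears as 1.57 (r = 0.5) or 2.04 (r = 0.7). The bias is zero if depression has no effect beyond the six mediators, and there is no ranking advantage if it correlates equally with all of them. A larger sample does not remove the bias where it exists. The point affects the interpretation of Aim 2 only and leaves the Aim 1 comparison of arms untouched.

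**What to change.** - Add baseline CESD as a covariate in the level-1 Aim 2 model. A baseline value cannot be a consequence of later stress, so this adjustment carries little risk.
- Pre-specify a sensitivity analysis that enters CESD at the same waves as the other mediators, as a seventh parallel mediator. Report the stress path and all relative weights with and without it.
- State in advance how a discrepancy is read. If the rank of stress changes, report its contribution as not separable from that of depression, and note that depression may also be a consequence of stress.

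The cost is plan wording and a little more analysis. CESD is already in the assessment battery. The Measures section gives one schedule for data collection, so this assumes CESD is taken at every wave. In the seven-variable model the standard error of the stress path is larger, by about 25% at the assumed correlation of 0.6.
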